### Statistical analysis

The power analyses in both trial-based economic evaluations will be based on the RCTs. The primary (base-case) analyses will be performed according to the intention-to-treat principle. This means that data from all participants will be used, regardless of whether they received the intervention or not. For the analyses we will use SPSS statistical software and Excel.

Respondents for whom at least 75% of the data per measurement instrument are available will be included in the analysis. Missing data on item level will be handled using SPSS missing value analysis. Completely missing measurements will be handled using multiple imputation (MI). A baseline analysis will be performed to examine the comparability of groups at baseline for both costs and outcomes. If necessary, methods will be applied to control for differences in baseline [33]. Despite the usual skewed distribution of costs, the arithmetic means is generally considered the most appropriate measure for describing cost data [33]. Therefore arithmetic means (and standard deviations) will be presented. In case of skewed cost data, non-parametric bootstrapping will be used to test for statistical differences in costs between the intervention and control group. Non-parametric bootstrapping is a method based on random sampling with replacement based on the participants' individual data [34]. The bootstrap replications will be used to calculate 95% confidence intervals around the costs (95% CI), based on the 2.5 and 97.5 percentiles. If cost data are distributed normally, t-tests will be used.

ICERs will be calculated for both the CEA and CUA. The ICER will be calculated as follows: ICER = (Ci - Cc)/(Ei - Ec), where Ci is the annual total cost of the new intervention, Cc is the annual total cost of the comparator, Ei is the effects at the 6 month follow-up for the new intervention and Ec is the effect at 6 month follow-up for the comparator.

The robustness of the ICER will be checked by non-parametric bootstrapping. Bootstrap simulations will also be conducted in order to quantify the uncertainty around the ICER, yielding information about the joint distribution of cost and effect differences. The bootstrapped cost-effectiveness ratios will be plotted subsequently in a cost-effectiveness plane, in which the vertical line reflects the difference in costs and the horizontal line reflects the difference in effectiveness. The choice of treatment depends on the maximum amount of money that society is prepared to pay for a gain in effectiveness, which is called the ceiling ratio. Therefore, the bootstrapped ICERs will also be depicted in a cost-effectiveness acceptability curve, showing the probability that the intervention is cost-effective using a range of ceiling ratios.

In addition, to demonstrate the robustness of our base-case findings, a multi-way sensitivity analysis will be performed. In the sensitivity analysis uncertain factors of assumptions in the base-case analysis will be calculated in order to assess whether the assumptions have influenced the ICER, for example by varying cost-prices and volumes between minimum and maximum [34].

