***Other outcomes***													

UPCC^f^	p	p	p	p									

VAS^g^	s	s		s									

ECSI^h^	s	s		s									

PSDRS^i^					s	s	s	s					

GSES^j^	p	p	p	p									

GAS^k^					s	s	s	s					

^a^The cost questionnaire used in the cohort study is a short questionnaire (11 items) compared to the cost questionnaire used in the Self-Management and augmented CBT Study (19 items)

^b^5 Dimensional EuroQol

^c^Hospital Anxiety and Depression Scale

^d^Utrecht Scale for Evaluation and Regabilitation Participation (*Utrechtse Schaal voor Evaluatie en Revalidatie - Participatie*)

^e^Stroke Specific Quality of Life

^f^Utrecht Proactive Coping Competence list

^g^Visual Analogue Scale

^h^Expanded Caregiver Strain Index

^i^Post Stroke Depression Rating Scale

^j^General Self-Efficacy Scale

^k^Goal Attainment Scale

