### Cost analysis

The following cost categories will be distinguished and included in this study: intervention costs, costs for the health care sector, patient and family costs and costs outside the health care sector. Intervention costs will include all the costs that contribute to the development and administration of the SMI and Augmented CBT. Health care sector costs are related, for instance, to general practitioner (GP) visits, hospital visits and medication. Patient and family costs concern, for instance, travel costs, costs of informal care, productivity losses and home adjustments. Costs outside the health care sector will be measured as productivity costs.

To measure the actual use of resources, data will be obtained using combined sources (registrations by professionals and a cost questionnaire for the patients conducted at al measurement points, T0 - T3, of both the Self-Management study and the Augmented CBT study). Resources used relating to the interventions will be based on the registered time all professionals spent on the treatment. All use of resources by the patient and their family, within and outside the health care sector will be measured by means of a cost questionnaire which will continuously record volumes of utilization during the follow-up period. The cost questionnaire has been designed especially for the participants in both RCTs, based on existing questionnaires [30]. The questionnaire consists of 20 items and will cover three areas of expenses, namely expenses of (inability to perform) daily activities, expenses of health care consumption and expenses of help received (material and immaterial).

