### Outcome measure

For the purpose of the COI study, necessary cost information will be retrieved through a specially designed short cost questionnaire of 11 items covering the costs of psychosocial care after stroke. A simple questionnaire is preferred, for the purpose of the COI study; accordingly the questionnaire has been adapted from previous trial-based economic evaluations studies.

The questionnaire consists of 3 subscales: health care costs, productivity costs and costs of informal care. The dimension of health care costs is captured with 8 items, productivity costs with 2 items and costs of informal care with 1 item. Care received will be measured in absolute numbers, representing visiting times and hours, day and nights spent on health care services and informal care. Due to the fact that the questionnaire is adjusted to be disease-specific every time it is being used, no research has been done on the validity of this questionnaire for stroke research. Nevertheless, the validity of self-reported measurements has been proven earlier in a large multi-centre clinical trial [36].

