### Statistical analysis

Missing data and skewed data will be handled similar as in the economic evaluation study, hence respondents for whom at least 75% of the data per measurement instrument are available will be included in the analysis and missing data on item level will be handled using SPSS missing value analysis. Completely missing measurements will be handled using multiple imputation (MI). Arithmetic means will be used to describe cost data, and presented. In case of skewed cost data, non-parametric bootstrapping will be used to test for statistical differences in costs between the intervention and control group. The bootstrap replications will be used to calculate 95% confidence intervals around the costs (95% CI), based on the 2.5 and 97.5 percentiles. If cost data are distributed normally, t-tests will be used.

Concerning the cost measurements, a month of missing data exists between T2 and T3 and 6 months of missing data exists between T4 and T5. To deal with the issue we will use interpolation to construct new data points for these periods. This will be done by calculating mean cost data for the period of 6 months (T3) to 12 months (T4) post stroke and the period of 18 months to 24 (T5) months post stroke. These data will be used to estimate the period between 12 months to 18 months post stroke.

We will do a comparative analysis to estimate differences in costs between 1 year post stroke and 2 years post stroke. Additionally, we will compare cost outcomes and effect outcomes on the primary outcome scales. Furthermore, we will try to determine *high-cost users *and *low-cost users *of health care after stroke. In the latter analysis, *high-cost users *and *low-cost users *will be identified by specific patients' characteristics, costs being the dependent variable and patient characteristics being independent variables.

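### Missing questionnaire items are kept out of the planned multiple imputation; if they are filled once, cost intervals come out too narrow, modestly so for total cost

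*Protocol article*

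**What the plan says.** The Statistical analysis section for the two trial-based evaluations first sets an entry rule: "Respondents for whom at least 75% of the data per measurement instrument are available will be included in the analysis". It then splits missing data by type. For gaps inside a returned questionnaire, "Missing data on item level will be handled using SPSS missing value analysis". For questionnaires not returned at all, "Completely missing measurements will be handled using multiple imputation (MI". No algorithm or number of fills is given for the first type.

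The Statistical analysis section of the COI study adopts the same scheme, "Missing data and skewed data will be handled similar as in the economic evaluation study", and restates that "missing data on item level will be handled using SPSS missing value analysis".

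The instruments concerned are:
- **Trial cost questionnaire.** Cost analysis says "The questionnaire consists of 20 items and will cover three areas of expenses" and does not give the items per area. Footnote a of Table 1 gives 19 items.
- **COI cost questionnaire.** It has 11 items, 8 of them for health care. The Outcome measure section lists "productivity costs with 2 items and costs of informal care with 1 item".
- **EQ-5D.** It has five dimensions with three levels each, and utilities attach to the combined health state (Outcome measures).

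Intervals for skewed costs come from percentile bootstrapping of individual participant data. In the trials the bootstrap also feeds the cost-effectiveness plane and the acceptability curve. How imputation and bootstrap are combined is not stated.

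**The concern.** Multiple imputation is already in the plan because a filled value is not an observed one. The plan applies that reasoning to whole missing questionnaires and not to missing items, and gives no reason for the difference.

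The items are not interchangeable indicators of one scale. Each cost item has its own volume and price, so the items that were answered may say little about the one that was not. A missing EQ-5D dimension leaves the health state, and so the utility, undefined at that measurement.

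If each gap receives one value and the completed data are then bootstrapped, every resample treats that value as real. The spread that reflects not knowing it is lost, and the same holds for the t-test planned for normally distributed costs. At stake are the cost intervals in all three studies and, in the trials, the scatter on the cost-effectiveness plane and the slope of the acceptability curve.

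**Working it through.** The documents give no item-level missing rate and no interval width, so there is no plan figure to reproduce. The number of admissible gaps follows from the documents. The sizes rest on stated assumptions.

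**1. Gaps the 75% rule admits** (items minus 75% of items, rounded up)

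| Instrument | Items | Needed | May be missing |
|---|---|---|---|
| Trial cost questionnaire | 20 | 15 | 5 |
| Same, by Table 1 | 19 | 15 | 4 |
| COI cost questionnaire | 11 | 9 | 2 |
| EQ-5D | 5 | 4 | 1 |

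In the COI form informal care is 1 item and productivity is 2, so a respondent with 9 of 11 items can lack either category completely. For the trial form this cannot be shown, because the items per area are not given.

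**2. Effect on total cost if each gap is filled once**

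Assume that a category carries a share s of total-cost variance and is independent of the rest, that it is missing completely at random in a fraction f of respondents, and that it is filled with its mean.

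- Variance reported from the completed data: (1 − s) + s(1 − f)
- Correct variance: (1 − s) + s/(1 − f)
- Width ratio: the square root of reported over correct
- Coverage of a nominal 95% interval: 2Φ(1.96 × ratio) − 1

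Example with s = 0.5 and f = 0.10: √(0.950/1.056) = 0.949. With f = 0.20: √(0.900/1.125) = 0.894.

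| s | f | Width ratio | Coverage |
|---|---|---|---|
| 0.25 | 5% | 0.987 | 94.7% |
| 0.25 | 10% | 0.974 | 94.4% |
| 0.25 | 20% | 0.946 | 93.6% |
| 0.50 | 5% | 0.975 | 94.4% |
| 0.50 | 10% | 0.949 | 93.7% |
| 0.50 | 20% | 0.894 | 92.0% |
| 0.50 | 30% | 0.837 | 89.9% |

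**3. Effect on one cost category carried by one item**

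Let m be the fraction missing and R² the share of the item's variance that the other data predict.

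- Reported variance factor: (1 − m) + mR²
- Correct variance factor: R² + (1 − R²)/(1 − m)

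For m = 0.10 and R² = 0.2: √(0.920/1.089) = 0.919, coverage 92.8%. For m = 0.20 and R² = 0.2: √(0.840/1.200) = 0.837, coverage 89.9%. With R² = 0 the ratios are 0.90 and 0.80, with coverage 92.2% and 88.3%.

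**4. Simulation of the planned bootstrap**

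The set-up was 53 per arm (the recruitment figure), two equal lognormal cost components correlated 0.3 on the log scale, one of them partly missing, 1,500 repetitions and 400 resamples. Coverage of the 95% percentile interval for the cost difference was:

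| Missing | One regression fill | One fill plus random residual |
|---|---|---|
| 10% | 91.3% | 91.4% |
| 20% | 91.4% | 90.4% |
| 30% | 88.5% | 90.1% |

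Complete data gave between 92.3% and 93.7%. The Monte Carlo standard error is about √(0.92 × 0.08/1500) = 0.7 percentage points, so the 10% row alone shows little. The loss is clear at 30%, and adding a random residual to a single fill does not remove it.

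**The case against.** The strongest reply is that the single fill is not in the text. The article names a software procedure without an algorithm, and such detail can sit in an analysis plan that is not shown. That stands as a limit: the conclusion must be conditional. It does not dispose of the point, because the article does fix the split, states it for the trials and again for the COI study, and names multiple imputation for one side only.

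Some stronger readings are tempting but not supported:

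- **A whole cost category is lost in the trials.** The item counts show this for the COI form only. Trial intervention costs also come from time registered by professionals, so questionnaire gaps do not touch them.
- **Coverage falls to about 90% for the reported costs.** The 89.9% and 88.3% in step 3 are for one component at 20% missing. For total cost the loss is smaller. It shrinks further when an item is missed at one visit only, since annual cost sums several measurements.
- **QALY intervals are too narrow by a known amount.** No figure supports this. At most one dimension per measurement is filled, and wholly missing EQ-5D measurements go to multiple imputation.
- **Fills will be negative or fractional, or the multiple imputation will be built on smoothed data.** Neither the algorithm nor the order of the two steps is given.

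The planned multi-way sensitivity analysis varies prices and volumes between extremes. It probes dependence on uncertain volumes but does not restore the lost interval width.

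A practical objection also stands in part. Twenty cost items and five EQ-5D items at four time points make (20 + 5) × 4 = 100 variables for 106 patients, so a full item-by-item model may not be feasible.

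**Conclusion.** The point holds in conditional form. The plan keeps item gaps out of its own multiple imputation while the 75% rule lets up to a quarter of an instrument be missing. If those gaps are filled once, which is the natural reading, cost intervals are too narrow. The direction is certain under a single fill.

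The size is modest for total cost: about 1% to 5% of width at up to 10% missing in a category carrying up to half the variance, and about 11% at 20%. For a category resting on one item, such as informal care in the COI study, it is about 8% to 10% at 10% missing and 16% to 20% at 20%. These figures assume the missing rates, variance shares and R², and missingness completely at random. The documents supply none of these. The QALY effect is real in kind but small in scope and unquantified.

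This does not undermine the evaluations. It should be changed because a better method is already in the plan.

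**What to change.** In both trials and the COI study, move missing cost items and missing EQ-5D dimensions into the multiple imputation already planned. Impute at item level where the model can support it, and otherwise at the level of cost category and EQ-5D utility. Use a method suited to skewed costs with many zeros.

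Compute total costs, and QALYs where they are used, within each imputed dataset. State how imputation and bootstrap are combined, so that imputation uncertainty reaches the cost intervals and, in the trials, the cost-effectiveness plane and the acceptability curve. Keep SPSS missing value analysis for describing the extent and pattern of missingness only.

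The cost is revised wording, more computing, and some reduction of the imputation model given 106 patients per trial. No extra data collection is needed.

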***Primary outcomes Restore4Stroke***													

EQ-5D^b^	s	s	s	s	s	s	s	s		s	s	s	s

HADS^c^	s	s		s	p	p	p	p	s	s	s	s	s

USER-P^d^	s	s		s	s	s	s	s	p	p	p	p	p

SS-Qol-12^e^	s	s		s	s	s	s	s		s	s	s	s

Life satisfaction	s	s		s	s	s	s	s		s	s	s	s

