### Outcome measures

In Figure 2 the outcome measures of the Restore4Stroke program in general and the four studies embedded in this program are shown. The primary outcome measure for the CEA will be the increase in health status as measured by the UPCC (Self-Management study) and the HADS (Augmented CBT study). Within the CUA, the primary outcome measures are QALYs for which an indirect preference-based technique will be used. In this technique, the patient's health status will be measured by means of the EQ-5D and weights that incorporate preferences from a general population sample will be used to calculate utilities. The EQ-5D is chosen because it is a widely used quality of life instrument (nationally and internationally). The EQ-5D contains five dimensions of health-related quality of life; namely mobility, self-care, daily activities, pain-discomfort and depression/anxiety [17]. Each dimension can be rated at three levels: no problems, some problems and major problems. The five dimensions can be summed into a health state. Utility values can be calculated for these health states, using preferences elicited from a general population, the so-called Dolan algorithm [26]. The utility values derived from the Dolan algorithm will be used to compute QALYs. The Dolan algorithm has been established using a general population from the UK. In 2006, a Dutch algorithm became available [27] using Dutch tariffs instead of UK tariffs to compute QALYs.

The utilities at the three time points will be used to compute a QALY score by means of the area under the curve method. Furthermore, the EQ-5D consists of a visual analogue scale (VAS) ranging from zero (worst imaginable health state) to 100 (best imaginable health state). The reliability and validity of the EQ-5D has been studied and established [28,29]. The base case analysis will use the individual utility score of the patient based on the EQ-5D.

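### Adjusting for baseline only when a comparability check suggests it gives up precision; always adjusting for the T0 values already collected is a free improvement

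*Protocol article*

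**What the plan says.** The rule is in the Protocol article, Statistical analysis, for the Self-Management and Augmented CBT evaluations. The check comes first: "A baseline analysis will be performed to examine the comparability of groups at baseline for both costs and outcomes". The consequence follows: "If necessary, methods will be applied to control for differences in baseline". The article gives no criterion for necessity, and names no covariate or model.

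The contrasts described around it are unadjusted as written. For skewed costs, "non-parametric bootstrapping will be used to test for statistical differences in costs between the intervention and control group", with t-tests if costs are normally distributed. The ratio is given as "ICER = (Ci - Cc)/(Ei - Ec"), and the cost-effectiveness plane and acceptability curve are built from bootstrapped versions of it.

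The baseline values exist. Cost analysis describes "a cost questionnaire for the patients conducted at al measurement points, T0 - T3" in both RCTs. Table 1 marks the EQ-5D ("EQ-5D^b^ s s s s s s s s") and the HADS ("HADS^c^ s s s p p p p") at T0 in both RCTs, and the UPCC at T0 in the Self-Management study only. On QALYs, Outcome measures says: "The utilities at the three time points will be used to compute a QALY score", by the area under the curve.

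**The concern.** A baseline covariate is worth adjusting for because it predicts the outcome, not because the arms happen to differ on it. A rule that waits for a visible difference has three costs.

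- **Precision.** In most trials no adjustment would be triggered, so the variance that the T0 value could explain stays in the estimate.
- **Chance imbalance.** A gap too small to be judged important still carries through to follow-up utility, costs, UPCC or HADS, in proportion to the correlation.
- **Choice of result.** Whether the base-case ICER is the adjusted or the unadjusted one is settled after the data are seen, on an unstated criterion.

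This matters in trials of 53 per arm, where cost and QALY differences are likely to be imprecise in any case.

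**Working it through.** **Inputs from the Protocol article (Sample size calculation).** Standardised difference .6 on the UPCC, rounded from .2/.35 = .57; 80% power; 45 evaluable per arm; 15% drop-out; 2 × 53 = 106 recruited. The same total is used for the Augmented CBT study.

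**Assumed inputs (not in the documents).** Baseline-outcome correlation r = .3, .5, .7; utility SD .25, range .20 to .30; two-sided alpha .05.

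**1. The plan's own figure.** n per arm = 2(1.96 + .84)²/.6² = 43.6, so 44, against 45 stated. 45/.85 = 52.9, so 53 per arm and 106 in total, as stated. The printed alpha of .5 would give 13 per arm, so two-sided .05 is evidently what was used.

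**2. Precision from adjustment.** The residual variance factor is 1 − r². Power is from the t distribution at 45 per arm, with d = .57 replaced by d/√(1 − r²).

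| r | variance removed | 106 patients worth, 106/(1 − r²) | UPCC power |
|---|---|---|---|
| unadjusted | – | 106 | 76% |
| .3 | 9% | 116 | 80% |
| .5 | 25% | 141 | 87% |
| .7 | 49% | 208 | 96% |

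**3. Chance imbalance in utility, 53 per arm.** SE = SD × √(2/53).

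| SD | SE | P(gap above .05 in either direction) | 1.96 × SE |
|---|---|---|---|
| .20 | .039 | 20% | .076 |
| .25 | .049 | 30% | .095 |
| .30 | .058 | 39% | .114 |

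The last column is the smallest gap that would trigger adjustment if the rule were applied as a 5% test. That reading is an assumption; the article names no test.

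**4. From utility gap to QALYs.** Take a 12-month curve at 0, 3, 6 and 12 months (Self-Management study), with equal SDs and equal correlations between all visits. The trapezoid weights are .125, .25, .375 and .25. A baseline gap g shifts the expected unadjusted QALY difference by g × (.125 + .875r). For g = .05:

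- r = .3: .05 × .3875 = .019
- r = .5: .05 × .5625 = .028
- r = .7: .05 × .7375 = .037

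The direct contribution of T0 is only .05 × .125 = .006; the rest comes through correlation with later visits.

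**5. The conditional rule itself.** Simulation with 40,000 runs, 45 per arm, normal data, and adjustment only if baseline p < .05 (again the assumed reading).

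| r | power at d = .6, conditional | power at d = .6, always adjusted | type I error, conditional | type I error, always adjusted |
|---|---|---|---|---|
| .3 | 81% | 83% | 4.8% | 5.0% |
| .5 | 81% | 89% | 4.2% | 5.0% |
| .7 | 82% | 98% | 3.7% | 5.0% |

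Unadjusted power in the same simulation was 80% to 81%, so the conditional rule recovers little of the gain.

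**The case against.** The strongest reply is that the plan is valid as it stands. Under randomisation the unadjusted difference is unbiased on average, the bootstrap interval already includes the variability from chance imbalance, and the simulated conditional rule did not inflate type I error. The authors also commit to checking baseline and to acting on what they find. All of this stands. It limits the point to efficiency and pre-specification, but it does not make the conditional rule preferable.

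A second reply is that criterion and model may sit in a fuller plan. That is fair for the detail. The conditionality, however, is stated in the article, and a threshold added elsewhere would still leave the choice to the data.

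Several stronger readings are tempting and are not supported:

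- **That a 5% test governs the check.** No test is mentioned; a descriptive judgement could trigger adjustment at smaller gaps.
- **That T0 utility is certainly the first point of the QALY curve.** The text speaks of three measurements while Table 1 shows four, so its role is unclear. T0 utility is a useful covariate either way.
- **That chance gaps are as large as the QALY gain to be expected.** The documents give no expected gain, and a utility gap is not a QALY difference.
- **That adjustment removes imbalance entirely.** Regression removes the modelled linear part, which is a real limit for skewed costs.
- **That the clinical UPCC or HADS tests are unadjusted.** The article refers other aspects of the RCTs to separate publications. The UPCC power figures therefore illustrate the gain and are not a verdict on those tests.

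**Conclusion.** The point holds as a free improvement, not as an error that invalidates the analysis. The article fixes a rule that is inferior to always adjusting, although the T0 values needed are already collected. The loss is 9% to 49% of the variance for r between .3 and .7; for costs, r may be at or below the low end. Chance gaps in baseline utility above .05 are common at this size: 30% of trials at SD .25, 20% to 39% over the SD range. On the assumed 0/3/6/12-month curve, such a gap moves the unadjusted QALY difference by about .02 to .04.

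The sizes rest on assumed values of r and SD. The direction does not depend on the exact values: with any material correlation, adjustment gains precision. That the base case is left to a judgement made after seeing the data follows from the text alone. A reader might infer that the unadjusted results would be biased; the documents do not support that.

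**What to change.** Replace the conditional sentence with one pre-specified base case, applied whatever imbalance is observed:

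- QALYs regressed on arm and T0 EQ-5D utility;
- costs regressed on arm and T0 costs;
- UPCC (Self-Management) or HADS (Augmented CBT) regressed on arm and its own T0 value.

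Fit these models within each bootstrap replicate, so that the ICER, the cost-effectiveness plane and the acceptability curve all use adjusted differences. Report baseline comparability descriptively only, with no influence on the choice of model. The unadjusted contrast can be shown as a sensitivity analysis. State at the same time whether T0 utility enters the area under the curve.

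The cost is a sentence or two in the plan and a small amount of programming. No additional data or patients are needed.

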### Timeline

For the Self-Management study, eligible patients and their informal caregivers will be randomized towards the Self-Management Intervention (SMI) or education intervention after baseline measurement T0. Both SMI and education intervention have a duration of 10 weeks and post-treatment measurement (T1) will take place at 3 months after T0. Two follow-up measurements (T2 and T3) will take place at 6 and 12 months after T0. For the Augmented CBT study, eligible patients will be randomized towards the Augmented CBT intervention the computerized cognitive training intervention after baseline measurement T0. Post-treatment measurements (T1) will take place 4 months from T0, and two follow-up measurements (T2 and T3) will take place 10 and 16 months from T0. Cost measurements for both studies are presented in Figure 3. At all measurement points, cost data will be asked retrospective varying from 2 to 6 months retrospective.

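### The ICER divides annual costs by effects at a 6-month follow-up, so costs and effects cover different periods in both trials

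*Protocol article*

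**What the plan says.** All references are to the protocol article.

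- **Statistical analysis (trial-based economic evaluations).** The scope is "ICERs will be calculated for both the CEA and CUA". One formula follows, the cost difference over the effect difference. On the intervention side it reads "where Ci is the annual total cost of the new intervention"; the next terms are "Cc is the annual total cost of the comparator, Ei is the effects at the 6 month follow-up for the new intervention"; and the last is "Ec is the effect at 6 month follow-up for the comparator". The section serves both trials and has no trial-specific version.
- **Timeline, Self-Management.** "post-treatment measurement (T1) will take place at 3 months after T0", then "Two follow-up measurements (T2 and T3) will take place at 6 and 12 months after T0".
- **Timeline, Augmented CBT.** The post-treatment measurement T1 is 4 months from T0, and "two follow-up measurements (T2 and T3) will take place 10 and 16 months from T0". Cost recall periods vary from 2 to 6 months.
- **Outcome measures.** "The primary outcome measure for the CEA will be the increase in health status as measured by the UPCC" for Self-Management, and by the HADS for Augmented CBT. QALYs are an area under the utility curve over three time points. Table 1 lists the EQ-5D at four (T0 to T3) in each trial.
- **Valuation.** Discounting is set aside on the ground that follow-up is shorter than one year.

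**The concern.** An ICER is interpretable only if the extra cost and the extra effect belong to the same period. Here the numerator runs for a year and the denominator is tied to six months. QALYs accumulate with time, so cutting them off earlier than the costs shrinks the denominator and changes the cost per QALY directly. Such a ratio cannot be read against a ceiling ratio.

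The same formula underlies the cost-effectiveness plane and the acceptability curve, so the main economic result of both trials is affected. In Augmented CBT the formula also names times that are not visits when counted from T0. The analyst would have to choose a visit and a way of building an annual cost. If that choice is made after the data are seen, the horizon can be picked by its result.

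**Working it through.** The plan states no utility or cost values and no ICER, so there is no figure to reproduce. The check compares schedules and then sizes the QALY effect under assumed profiles.

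**1. Formula times against visits (months)**

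| Trial | Visits from T0 | Visits from T1 | Month 6 from T0 a visit? | Month 12 from T0 a visit? |
|---|---|---|---|---|
| Self-Management | 0, 3, 6, 12 | 0, 3, 9 (T1–T3) | yes (T2) | yes (T3) |
| Augmented CBT | 0, 4, 10, 16 | 0, 6, 12 (T1–T3) | no | no |

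Counted from T0, only Self-Management has a 6-month visit. Counted from T1, only Augmented CBT has one. No single origin serves both trials, and under either origin a year of cost is paired with an effect at six months.

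**2. Annual cost in Augmented CBT**

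If cost windows run from visit to visit (an assumption, since Figure 3 is not available), month 12 lies inside the T2–T3 window. An annual cost then needs (12 − 10)/6 = one third of that window, or scaling of the 16-month total by 12/16 = 0.75. These agree only if costs are spread suitably over time. The article does not say which applies.

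**3. QALY effect**

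Assumptions: QALYs stop at the 6-month follow-up; the between-group utility gain rises linearly from 0 at T0 to d at T1 and then stays at d; incremental cost is positive. Area is in years, by trapezoids. Overstatement = QALY gain to month 12 ÷ QALY gain to the effect time point.

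Self-Management:
- To month 6: ½ × 3/12 × d + 3/12 × d = 0.125d + 0.25d = 0.375d
- To month 12: 0.375d + 6/12 × d = 0.875d
- Ratio: 0.875/0.375 = 2.33
- If the gain fades linearly from d at T2 to 0 at T3: 0.375d + ½ × 6/12 × d = 0.625d, ratio 0.625/0.375 = 1.67

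Augmented CBT:
- To month 6 (interpolated): ½ × 4/12 × d + 2/12 × d = 0.333d
- To month 10 (T2): 0.167d + 6/12 × d = 0.667d
- To month 12: 0.167d + 8/12 × d = 0.833d
- Ratio: 0.833/0.333 = 2.5 if month 6 is meant, or 0.833/0.667 = 1.25 if T2 is meant

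Sensitivity to the profile: a gain constant from T0 gives 2.0 in Self-Management, and 2.0 (month 6) or 1.2 (T2) in Augmented CBT. A gain that peaks at T1, halves by T2 and is zero at T3 gives 1.4 in Self-Management, and 1.91 or 1.13 in Augmented CBT.

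**4. Clinical scores (CEA)**

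The UPCC and HADS are scores at a point in time. Let the difference be e at the 6-month follow-up and r × e at month 12. With annual cost in both, the plan's ratio divided by the matched 12-month ratio is (C/e) ÷ (C/(r × e)) = r. If r = 1 the two agree. If the effect fades (r < 1), the plan's ratio flatters the intervention. If it grows (r > 1), the plan's ratio penalises it.

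**The case against.** **The 6-month follow-up in Augmented CBT may mean T2.** This is plausible: the Timeline calls T1 post-treatment and T2 and T3 follow-up, and T2 is six months after T1. A reader might take 2.5-fold as the size in that trial, but the text supports only a range of 1.25- to 2.5-fold. The mismatch with annual cost remains under either reading.

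**The QALY horizon is ambiguous, not fixed at six months.** Three time points could be T0–T2 or a set that reaches T3. This stands, so the CUA figures are conditional on QALYs stopping at the 6-month follow-up. That is what the formula literally says.

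**An annual cost can be derived in Augmented CBT.** The Cost analysis section says resource use is recorded continuously over follow-up, so one should not infer that no such cost can exist. What holds is that month 12 is not a visit and no derivation rule is given.

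**The mismatch does not always work against a lasting benefit.** Correct. That inference holds only for accrued QALYs with positive incremental cost. For the UPCC and HADS, step 4 shows the bias can be nil or go either way.

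**The HADS sign is not wrong.** Because raw HADS scores fall with improvement, a reader might infer that the formula returns the wrong sign. The article does not support that: the Designs section expresses the ratio per point of improvement, and Outcome measures defines the effect as a gain in health status. Only the coding is left unstated.

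**Article brevity** does not cover the core point. The formula is explicit, and nothing shown reconciles it with the schedules.

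**Conclusion.** The point holds. The formula pairs annual costs with effects at a 6-month follow-up for both the CEA and the CUA. It leaves scheduled 12-month effects unused in Self-Management, and it cannot be applied to Augmented CBT without an unstated choice of visit and of cost derivation.

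In the CUA, with QALYs cut at the 6-month follow-up, positive incremental cost and a gain that rises to T1 and persists, cost per QALY is overstated about 2.3-fold in Self-Management (1.7-fold if the gain fades from T2 to zero at T3). In Augmented CBT it is overstated 1.25- to 2.5-fold by reading. The utility profiles are assumptions, because the article gives no utility data. In the CEA the fault is that costs run on past the effect; neither size nor direction can be given in advance.

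**What to change.** - State one horizon per trial, ending on a planned visit, and use it for costs, clinical effect and QALYs. T0–T3 is the natural choice: 12 months for Self-Management and 16 months for Augmented CBT. A shorter matched horizon would also cure the mismatch but would leave scheduled data out of the main result.
- Redefine Ci and Cc as total cost over that horizon. Redefine Ei and Ec as the UPCC or HADS effect at its end (CEA) and as QALYs accrued over it (CUA).
- Make any earlier-horizon ratio secondary, with its costs cut at the same visit.
- In Outcome measures, replace the three QALY time points with the four EQ-5D visits in Table 1.
- In Valuation, correct the statement that follow-up is under a year, and restate the discounting decision for the horizon chosen; 16 months runs into a second year.
- State that the HADS effect is coded as the reduction in score.
- Confirm that the cost recall windows cover the whole horizon, or give a rule for any gap.

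Cost: wording only. The cost questionnaire, EQ-5D and each trial's primary scale are already scheduled at T0–T3, and the Current study status section says data collection has yet to start.
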